### Equipment and technology

To collect medium-term HRV data, participants will wear a Fitbit Charge 5 smartwatch for a total of 6 weeks. The HRV-B itself will be conducted using a Polar H10 chest strap for 10 min two times per day. This connects via Bluetooth to the Elite HRV smartphone app, which is downloaded to participants’ phones. Participants will aim to increase their HRV score as displayed in Elite HRV in real time using a diaphragmatic breathing technique (figure 1). Omron M2 blood pressure monitor (endorsed by the British Hypertension Society) will be used to conduct NLT in clinic and the adapted Autonomic Profile (aAP).^27^

**Figure 1 F1:**
[figure not shown]
Heart rate variability biofeedback (HRV-B) using a breathing technique and chest strap for real-time HRV monitoring. Polar H10 picture from Wikimedia commons, reprinted under CC BY-SA 3.0 license. EliteHRV screenshot from Wikimedia commons, reprinted under CC BY-SA 4.0 license.

### Study phases

The study will be carried out in the following three phases:

Pre-HRV-B phase.HRV-B phase.Post-HRV-B phase.

### Pre-HRV-B phase

The participant will either be invited to a research clinic or visited at their home by a member of the research team (first appointment A1). They would have already received the participant information sheet (PIS) at screening and would have had more than 24 hours to read and understand the content of the PIS. Written consent will be signed by the participant and the researcher during this first visit. Devices and baseline outcome measures used in this stage are:

Fitbit charge five device and the Fitbit smartphone application: The participant will be requested to have the Fitbit device on most of the time during the 6-week period. The application records HRV at night along with other measures of sleep (sleep stages, HR) and daytime activity (such as step count).C19-YRSm: the COVID-19 Yorkshire Rehabilitation Scale (C19YRS) is the literature’s first condition-specific patient recorded outcome measure, which has been validated in the LC population.^28 29^ The modified scale provides a symptom severity score (out of 30), functional disability score (out of 15), other symptoms score (out of 25) and overall health score (out of 10).^23^ The participant will complete C19YRSm (online supplemental file 1) at weekly intervals to monitor the impact of the intervention on LC symptoms. They will also have weekly telephone reviews with study researchers for troubleshooting and to ensure maximal compliance with the study.Composite Autonomic Symptom Score (COMPASS): the COMPASS 31 will be completed by the participant at the initial visit and again 6 weeks later at the end of the study. Autonomic symptoms are scored for different domains including orthostatic intolerance, vasomotor, secretomotor, gastrointestinal, bladder and pupillomotor. Total scores for each domain are multiplied by a set weighting and then added together to provide a score out of 100 representing severity of autonomic symptoms. A higher score represents greater severity.^30^aAP: this is an autonomic profile test developed by St Mary’s Hospital and the National Hospital for Neurology and Neurosurgery and later adapted for domiciliary use during the COVID-19 pandemic.^27^ Participants are asked to monitor their heart rate and BP on lying, and at 3 min of standing at various intervals over 24 hours, including after waking, after eating breakfast/lunch/dinner, before and after 5 min of exercise, and before bed (online supplemental file 2). Abnormal results are calculated using the same criteria for heart rate and BP differences as the NLT (HR increase >30/min or BP drop >20 mm Hg).WHO Disability Assessment Schedule (WHODAS): this is validated generic measure of functioning and disability. The 36-item scale captures six domains of life (cognition, mobility, self-care, getting along, life activities and participation) with a summary score ranging from 0 (no disability) to 100 (full disability)^31 32^EQ-5D-5L: The EQ-5D-5L instrument, provided by the EuroQol Group, is one of widely used quality of life measures, consists of five items covering: mobility, self-care, usual activities, pain/discomfort and anxiety/depression.^33^ The item scores can be converted into a total index score by applying health preference weights elicited from a general population. This index score can also be used in economic evaluations to assess the cost-effectiveness of health interventions.^34^

10.1136/bmjopen-2022-066044.supp1Supplementary data

10.1136/bmjopen-2022-066044.supp2Supplementary data

The A1 appointment will last approximately 2 hours and may be longer for those with cognitive fatigue or ‘brain fog’. If felt necessary, it will be divided into two 1-hour visits to reduce cognitive fatigue.

### HRV-B phase

One week after the A1 appointment, the participant will be either invited to attend a research clinic or visited at home by a researcher (second appointment A2) to commence the HRV-B study phase. This involves:

Polar H10 chest strap and Elite HRVB application: The participant will be familiarised with the technology and introduced to a paced breathing regimen via a one-to-one demonstration. They will be instructed to perform the breathing technique using the application at least two times a day, 10 min per session, for a period of 4 weeks. The chest strap device will record HRV for the duration of the session, and the data get recorded in the application. While this phase is ongoing, participants will continue to wear the Fitbit Charge 5 device for the duration of this phase.Fitbit charge 5 device and the Fitbit smartphone application.C19-YRSm.

### Post-HRV-B phase

The participant will be asked to stop the HRV-B intervention after completing 4 weeks of the treatment. They will be asked to continue using the Fitbit device for another week when not doing the intervention. They will then either be invited to a research clinic or be visited at home by a study researcher. At this appointment (A3), the participant will complete:

C19 YRSm: the C19-YRSm will be completed by the patient every week for a total of 6 weeks. There will be a total of 7 C19-YRS documents completed.Fitbit charge 5 device and the Fitbit smartphone application.NLT and aAP.COMPASS 31.WHODAS.EQ-5D-5L.

During the A3 appointment, the Polar H10 strap and the Fitbit device will be retrieved.

The participants will be invited to complete a further C19-YRS, by email or postal 4 weeks after completion aAP for 24 hours and to email or post the results to the study researcher.

### Outcome measures

*The primary outcome measure* is the C19YRSm, a self-reported patient-reported outcome measure to assess LC symptom severity, functional disability and overall health status.

*Secondary outcome measures* include:

Heart rate measures from chest strap:

7-day average HRV score out of 100—quantified by the Elite HRV app via the root mean square of successive differences between normal heartbeats (rMSSD). A natural log (ln) is applied to this figure and then expanded to generate a 1 to 100 score.Mean R–R interval.Heart rate.rMSSD.SDNN (SD of Normal to Normal intervals).Total power.Low-frequency power (LF).High-frequency power (HF).LF:HF ratio.

Fitbit data:

Sleep staging data.Resting heart rate.Daily activity levels, for example, step count and exercise type and duration.

Patient-reported outcome measures:

NLT and aAP.COMPASS 31.WHODAS.EQ-5D-5L.

During our final interaction with participants in the study, we will ask them the following questions to assess the feasibility of the study:

‘How did you find using the technology?’‘How did you find the breathing intervention?’‘Have you noticed any change in your symptoms?’

Their opinions and suggestions will be recorded as quotes in their participant files. However, we are not planning to undertake a formal qualitative analysis of responses as it is not one of the main objectives of this study.

A summary of the schedule for the completion of outcome measures is shown in table 1.

**Table 1 T1:** Outcome measures summary schedule

	Initial assessment Clinic	Pre HRV-B phase (1 week)	HRV-B phase (4 weeks)	Post HRV-B phase (1 week)
Autonomic screening (NLT)	√			√
Autonomic function (COMPASS 31)		√		√
Home autonomic test (aAP)	√			√
Fitbit wrist strap HRV, sleep data		√	√ daily	√
Polar H10 chest strap HRV data			√ daily	
LC-specific PROM C19-YRSm		√	√ weekly	√
Daily function (WHODAS)		√		√
Quality of life (EQ5D-5L)		√		√

aAP, adapted Autonomic Profile; COMPASS 31, Composite Autonomic Symptom Score; C19-YRSm, modified COVID-19 Yorkshire Rehabilitation Scale; EQ-5D-5L, EuroQol 5-Dimension 5-Level; HRV-B, heart rate variability biofeedback; LC, long COVID; NLT, NASA Lean Test; WHODAS, WHO Disability Assessment Schedule.

## Sample size

A formal sample size calculation is not required for a feasibility study as it does not mimic a definitive randomised trial and aim is not to measure effect size.^35^ A sample size of 30 is the average sample size across feasibility studies and is accepted as reasonable size to assess the acceptability and suitability of the intervention.^36^

## Statistical analysis

Quantitative data from standardised questionnaires will be scored as per standard procedures. Data downloaded from the wearable devices will be extracted, cleaned and summarised using specific software packages, including Matlab and Python. Quantitative data will be analysed with simple descriptive statistics. The presence and magnitude of pre and postintervention differences will be examined using repeated paired sample t tests (with Bonferroni adjustment for multiple comparisons), and the effect size will be explored using both Analysis of Variance (ANOVA) partial η^2^, and Cohen’s d. Additional exploratory analyses may also be performed to fully analyse the data set produced, guided by the findings of the descriptive statistics.

### Patient and public involvement

Members of the Patient Advisory Group (PAG) with lived experience of LC have been involved in the design, development and delivery of the project. Members of the PAG attended proposal research planning meetings and shared their experiences on symptoms of dysautonomia, which helped shaped the research question, design and outcome measures of this study. Members of this group have contacts with wider patient community groups and helped disseminate information about the study. The PAG meets quarterly with the research team to review progress, ensure the research continues to answer relevant issues and that findings can inform LC care. The group will be involved in the dissemination of research findings and writing lay summary reports that will be shared with the participants.

### Ethics and dissemination

The study has received ethical approval from Health Research Authority (HRA) Leicester South Research Ethics Committee (21/EM/0271). Informed consent will be obtained from all participants. Potential participants will have a minimum of 24 hours to review the PIS and discuss queries with the researcher prior to signing the written consent. General Data Protection Regulation (GDPR) rules will be strictly followed for all data gathered during the study. All data will be fully anonymised as soon as practical. All devices used are (Conformité Européenne (CE) marked and are being used for their intended purposes. There is potential for minor skin irritation from wearing the Fitbit and Polar H10 devices. This will be enquired about at each weekly telephone review.

For participants with cognitive fatigue or ‘brain fog’ relating to LC, the length of the appointments with the researcher (A1, A2 and A3) may be longer than normal. Supplementary written information will be provided, and if necessary, each of these appointments may be conducted in two shorter sessions to reduce information overload and possible impact on LC symptoms. Participants will be advised that they do not need to proceed with the appointments or the study if they do not want to. All appointments other than the initial NLT can occur at the participants’ homes to reduce travel and inconvenience. Participants are free to withdraw at any point in the study. They will be encouraged to give reasons for the withdrawal, but it will not be compulsory to give a reason for withdrawal.

Dissemination will include both academic publications and lay summaries in various formats. Academic outputs will include both medical and engineering literature. Policy impact will be aided by our strong existing links to NHS England and the UK Long COVID National Task Force. [name], who leads the NIHR project Long COVID Multidisciplinary consortium for Optimising Treatments and Services across the NHS (LOCOMOTION),^37^ is also an advisor for the WHO—Europe on COVID-19 rehabilitation and is also involved in the WHO working party developing a core set of outcome measures for LC.

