## Methods

### Study design

This is a phase 2 uncontrolled open-label feasibility study of a home technology-based HRV-B in 30 individuals with LC. Potential participants will be identified through the Leeds COVID-19 Rehabilitation Service, based at Leeds Community Healthcare NHS Trust. The study period will be 6 weeks for each participant. The study start date is 24 January 2022, and the anticipated end date is 31 March 2024.

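### The effect is tested on pre/post pairs with no provision for data from a participant who stops HRV-B early, so loss related to worsening would bias the estimate towards benefit

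*Protocol article*

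**What the plan says.** The Study design section states: "This is a phase 2 uncontrolled open-label feasibility study of a home technology-based HRV-B in 30 individuals with LC". The primary outcome "is the C19YRSm, a self-reported patient-reported outcome measure to assess LC symptom severity, functional disability and overall health status" (Outcome measures). Under Post-HRV-B phase, "the C19-YRSm will be completed by the patient every week for a total of 6 weeks", and that section puts the total at seven forms. COMPASS 31, WHODAS and EQ-5D-5L are scheduled only in the week before and the week after the intervention (Table 1).

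On analysis, the Statistical analysis section says: "The presence and magnitude of pre and postintervention differences will be examined using repeated paired sample t tests", with Bonferroni adjustment. Partial eta squared and Cohen's d serve as effect sizes.

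On leaving early, two sentences under Ethics and dissemination apply: "Participants are free to withdraw at any point in the study. They will be encouraged to give reasons for the withdrawal", with the reason optional, and "Participants will be advised that they do not need to proceed with the appointments or the study if they do not want to". The only planned end of the exercise, under Post-HRV-B phase, is completion of 4 weeks. The article does not say what is collected from a participant who gives up the exercise but has not left the study.

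The Strengths and limitations box says the efficacy estimate will determine the scope and sample size of a larger controlled trial. The Sample size section says "A formal sample size calculation is not required for a feasibility study" and that measuring effect size is not the aim.

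**The concern.** A paired t test needs a value after the intervention as well as before it. Anyone without the later value drops out of that comparison. If those people tend to be the ones who felt worse, the remaining pairs look better than the whole group. With no control arm, nothing inside the study would show that this had happened.

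Two things are at stake. The efficacy estimate is meant to size the next trial, and an inflated one would make that trial too small. Acceptability and compliance are also stated interests of the study, and the course of people who stop the exercise is part of the answer.

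**Working it through.** **Plan's own figures.** The sample size of 30 has no stated alpha, power, effect size, SD or dropout rate, so there is nothing to reproduce. The form count can be checked: 1 + 4 + 1 = 6 weeks, and forms at weeks 0 to 6 make 7, as stated.

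**Who has a pair.** Take a participant who leaves two weeks into HRV-B, at week 3.
- C19-YRSm: forms at weeks 0, 1, 2 and 3 can exist (4 of 7). Whether any of the later ones counts as the post value is not fixed.
- COMPASS 31, WHODAS, EQ-5D-5L: start value only, so no pair.

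**Size of the bias.** The document gives no dropout rate and no expected change, so the inputs below are assumptions. Units are SDs of change, and positive means improvement. With k leavers of 30:

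all-30 mean = [(30 - k) × completers' mean + k × leavers' mean] / 30

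bias = completers' mean - all-30 mean = (k/30) × (completers' mean - leavers' mean)

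| Completers | Leavers | Bias, k = 3 | Bias, k = 6 |
|---|---|---|---|
| +0.2 | -0.5 | 0.07 | 0.14 |
| +0.2 | -1.0 | 0.12 | 0.24 |
| +0.5 | -0.5 | 0.10 | 0.20 |
| +0.5 | -1.0 | 0.15 | 0.30 |

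**In scale points.** On the 30-point symptom severity score, assume completers improve by 3 and leavers worsen by 2. For k = 3, 6, 9 the all-30 mean is (27×3 - 3×2)/30 = 2.5, (24×3 - 6×2)/30 = 2.0 and (21×3 - 9×2)/30 = 1.5. The completers' figure is 3.0 each time. Required sample size varies as 1/effect², so at equal SD a trial sized on 3.0 would have (2.5/3)² = 69%, (2.0/3)² = 44% or (1.5/3)² = 25% of the participants needed.

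**When the sign reverses.** The completers' mean is positive and the all-30 mean negative only if the share lost exceeds completers' mean / (completers' mean - leavers' mean).
- +0.2 and -1.0: 0.2/1.2 = 16.7%, more than 5 of 30.
- +0.2 and -0.5: 0.2/0.7 = 28.6%, more than 8.6 of 30.
- +0.5 and -1.0: 0.5/1.5 = 33.3%, more than 10 of 30.
- +0.5 and -0.5: 0.5/1.0 = 50%, more than 15 of 30.

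**Simulation.** This used 20,000 trials of 30, change distributed N(true mean, 1), an unadjusted two-sided 5% paired t test, and the worst k removed. That is the most extreme selection for a given k.

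| True mean | Completers' mean, k = 3 | k = 5 | k = 6 |
|---|---|---|---|
| 0 | +0.19 | +0.29 | +0.34 |
| -0.2 | -0.01 | +0.09 | +0.14 |
| -0.3 | -0.11 | -0.01 | +0.04 |

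With a true mean of 0, nominally significant benefit appears in 2.4% of trials without loss, 21.5% with k = 3 and 53% with k = 6. Bonferroni adjustment would lower these rates. Under milder selection, where each participant with change below -0.5 SD leaves with probability 0.25, true means of 0, -0.2 and -0.3 become +0.10, -0.10 and -0.19. The estimate is shifted upwards but no negative mean turns positive.

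**The case against.** The strongest reply is that much of this rests on silence. Analysis populations and missing-data handling are commonly left to an SAP or full protocol, and neither is shown. The article does not say that stopping the exercise counts as withdrawal, that A3 measures are refused afterwards, or that data already given are discarded. It names declining appointments separately from leaving the study. It also plans descriptive statistics and, beyond the effect sizes "and Cohen’s d. Additional exploratory analyses may also be performed to fully analyse the data set produced". Weekly forms, weekly calls, requested reasons for withdrawal and closing questions all offer sight of someone who worsens.

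Most of this stands. The absence of a missing-data policy is not the point made here, and the weekly scores before exit could be used. Two things remain. The one test the article names works on pairs, and even a separate comparison at each week would omit those already gone. Whether people who stop are asked for further data is also settled when data are collected, and no analysis plan can recover A3 measures that were never sought.

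Loss could also come from burden, trouble with the technology or improvement. The bias would then be smaller, absent or in the other direction.

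**Conclusion.** The point holds as a conditional one. If loss is related to worsening, the paired analysis overstates benefit, and the single-arm design cannot reveal it. On the assumptions shown, the inflation is 0.07 to 0.15 SD with 3 of 30 lost and 0.14 to 0.30 SD with 6 lost. The true size is unknown, because the document gives no dropout rate and no evidence that HRV-B worsens anyone.

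The exposure is plainest for COMPASS 31, WHODAS and EQ-5D-5L, which would have no pair. For C19-YRSm, scores before exit exist but are not clearly used in the named test.

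A reader might infer that people who get worse disappear from the results and that harm would be reported as benefit. The document does not support that. Weekly C19-YRSm scores remain up to exit, nothing says they are discarded, and in the scale-point example every all-30 mean is still an improvement. Reversal needs substantial outcome-related loss: from more than 5 to more than 15 of 30 in the mixtures above.

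**What to change.** Under Ethics and dissemination, separate stopping the exercise from leaving the study. State that participants who stop HRV-B are invited, unless they decline, to continue the weekly C19-YRSm and the A3 questionnaires, remotely if preferred.

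Under Statistical analysis, analyse C19-YRSm change with a repeated-measures mixed model using all weekly scores from every participant who started HRV-B, and keep the paired t test as supportive. Report the number who stopped, with reasons where given, and the number whose last available score is worse than baseline.

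The model corrects only for decline that shows in a form returned before exit, so the invitation to keep giving data matters more than the choice of model.

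The cost is amendment wording, one model and one table. The forms, calls and A3 visit already exist. The reported effect may be smaller, and some who stop will still decline follow-up. The change concerns data collection and analysis only, and sets no rule for when HRV-B should be stopped.
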